## Abstract

**Background:**

Smoking is one of the leading preventable causes of illness and premature death worldwide. Despite a variety of effective treatments, relapse rates remain high, and novel, innovative interventions are needed in order to reduce the global prevalence of smoking. Research has indicated that deficits in the ability to inhibit a response (referred to as response inhibition) is a predictor of relapse and subsequently, targeting this potentially modifiable risk factor may lead to improvements in smoking outcomes. Indeed, in recent years, stimulus-specific response inhibition training has emerged as a potentially efficacious intervention to reduce unwanted/unhealthy behaviours such as alcohol and unhealthy food consumption. As such, the present trial is the first to evaluate the real-world efficacy of response inhibition smoking training (INST) in a sample of adult heavy smokers.

**Methods/design:**

This randomised controlled trial will recruit nicotine dependent smokers aged between 18 and 60 using social media and advertisements in Victoria, Australia. The sample target was 150 to account for drop out and non-adherence. Once informed consent has been obtained, participants complete a range of baseline measures during a face to face interview. Participants are randomly allocated to one of two online training conditions: an intervention training group (INST), which requires participants to exercise response inhibition towards smoking-related stimuli; or an active control group, which requires participants to exercise response inhibition towards household items and does not include any smoking-related stimuli. They complete the first training session during the interview to ensure the training protocol is clear. Both groups are instructed to complete a further 13 training sessions (1 per day) at home on their computer and follow-up phone calls will be conducted at three time points: post-intervention, one-month and three months. The primary outcomes are: a) rates of smoking cessation and; b) reduction in the quantity of average daily smoking at post-intervention, one and three months follow-up.

**Discussion:**

There is a pressing need to develop novel and innovative smoking interventions. If proven to be effective, INST could make a highly cost-effective contribution to improvements in smoking intervention outcomes.

**Trial registration:**

The trial was prospectively registered with the Australian New Zealand Clinical Trials Registry 17th February 2017. Trial ID: ACTRN12617000252314.

**Electronic supplementary material:**

The online version of this article (10.1186/s12889-018-6109-y) contains supplementary material, which is available to authorized users.

## Background

Tobacco smoking is one of the leading preventable causes of illness and premature death worldwide. It is the second largest contributor to the burden of disease globally, with 134.2 million years lost to disability, illness and premature death [1]. In 2013, 6.1 million people died globally as a result of tobacco use [1], and, if trends persist, this number will exceed 8 million by the year 2030 [2]. Furthermore, tobacco use has been found to cost the global economy more than US$1 trillion each year in healthcare expenditures and lost productivity [3]. As smoking remains at unacceptable levels across the world [4, 5], examinations of effective and accessible smoking cessation treatments are crucial in reducing the global burden of smoking on public health.

Currently, pharmacological and psychosocial interventions have the most support as efficacious treatments for the cessation of smoking [6–10]. However, despite the positive outcomes associated with these interventions, most smokers do not seek formal treatment to reduce smoking [11] and existing treatments can entail several limitations. First, smokers have reported concerns regarding adverse side-effects of pharmacological treatments which have impacted treatment uptake and long-term adherence [12–14]. Second, the long-term cost of pharmacological and psychosocial interventions, which can be more expensive than cigarettes themselves, often prohibit individuals from accessing smoking cessation treatments. This is particularly relevant given that: 1) the financial costs of tobacco are one of the primary reasons underpinning quit intentions and attempts [4, 15, 16] and; 2) the incidence of smoking is increasing most rapidly in developing nations who have the lowest levels of disposable income [5]. Therefore, there is a critical need for accessible and cost-efficient interventions for smoking cessation. Third, relapse rates remain consistently high following treatment [17] and, the vast majority will relapse within five to 10 days of treatment cessation [18, 19]. Thus, a substantial proportion of individuals attempting to quit smoking fail to achieve long-term abstinence, inviting the question: what modifiable risk factors for smoking relapse may be targeted to increase abstinence rates or at the very least result in reduction of level of smoking?

Previous research indicates that deficits in response inhibition are a strong predictor of relapse for smokers following a quit attempt [20, 21]. Research suggests that recently abstinent smokers experience heightened difficulties with response inhibition [22, 23], indicating that targeting this may assist in preventing relapse. Importantly, a meta-analysis [23] supports evidence showing that individuals dependent on substances such as cocaine and alcohol may experience deficits in response inhibition. Furthermore, Yin and colleagues [24] found that a group of smokers reported response inhibition deficits on the GNG task. Taken together this provides some evidence that smokers may experience difficulties with response inhibition. Of significance is that individuals who reported higher nicotine dependence experienced greater deficits in response inhibition than those of lower use or dependence [25, 26]. Given that heavier smokers find it more difficult to quit [27, 28], response inhibition deficits may be an effective target for treatment in these individuals.

Indeed, response inhibition training interventions utilising tasks such as the go/no-go (GNG) task and stop signal task (SST) focus on training successful inhibition of a habitual or pre-potent response by pairing pictorial cues of the targeted behaviour with stop signals or no/go cues [29]. The GNG task targets automatic bottom-up response inhibition (or action restraint) by consistently pairing no-go cues with the target stimuli [30, 31], while the SST targets top-down inhibitory control (or action cancellation) as stop signals occur after an initiated response and are mapped only to a proportion of target stimuli [32]. These tasks have recently been examined to reduce alcohol and food intake, yielding efficacious results [33]. For example, Houben, Havermans, Nederkoorn, and Jansen [34] randomly assigned 57 heavy alcohol drinkers to receive one of two training conditions: a beer/no-go condition, where alcohol-related stimuli were consistently paired with a stopping response, or a beer/go condition, where participants always responded to alcohol-related stimuli. Compared to participants in the beer/go condition, those who were trained to inhibit their response towards alcohol-related stimuli (beer/no-go) reported significantly less alcohol intake. Similar findings were reported by Jones and Field [35]. In their study, following motor inhibition training utilising a modified SST, heavy social drinkers were found to consume significantly less alcohol in a subsequent ad libitum taste test.

More recently Lawrence et al. [36] implemented an internet-delivered response inhibition training intervention for food among 83 overweight and obese adult participants. Participants were randomly allocated to receive four 10-min training sessions completed online. In the intervention group, high-calorie foods were consistently paired with no-go signals and in the control group, non-food stimuli were consistently paired with no-go signals. At one-week follow-up, participants in the food no-go condition consumed significantly less food, showed significant weight loss, and had decreased positive evaluations towards high calorie foods compared to controls. At 6 month follow-up, participants in the intervention group displayed significantly higher average weight loss (2.21 kg) compared to controls (0.36 kg). These findings are consistent with a previous trial [37] that compared two interventions for losing weight: an implementation intention intervention that instructed participants to plan reminders for dieting and a response inhibition intervention that paired no-go responses with food-related stimuli. Findings indicated that participants who completed only the response inhibition training reported significant weight loss after four training sessions. Together, these results indicate that response inhibition training can be effectively delivered online, promoting greater accessibility and cost-efficiency of these types of interventions.

Two meta-analyses have found that inhibitory control training resulted in an overall significant effect (albeit a small effect size), with GNG training yielding larger (medium) effect sizes than SST training [29, 33]. According to the Behaviour Stimulus Interaction (BSI) theory [38] behavioural changes induced by the GNG training are mediated by changes in evaluations of the stimuli used in the task. That is, positively regarded stimuli will become associated with negative affect as a result of consistently being paired with no-go cues. This is thought to devalue the stimuli and minimise the likelihood of approach behaviours occurring towards the stimuli in real life. This theory has been supported by evidence in studies targeting alcohol consumption that suggest a mediating effect of changes in implicit attitudes on alcohol intake [34, 39]. In the food domain, there is evidence of devaluation of trained no-go food stimuli as assessed by visual analogue scales [36, 40, 41]. Another proposed mechanism of response inhibition training is the automatic inhibition hypothesis (AIH) [32], which posits that automatic response inhibition can develop over practice if stimuli are consistently associated with stopping [42, 43]. These two potential mediating hypotheses will be investigated in this trial.

In summary, given that significant effects of the GNG task were found despite the use of non-clinical samples, it was expected that these interventions would be particularly effective with smokers as smoking receives the most frequent reinforcement compared with other dependent populations, with multiple smoking sessions each day. Furthermore, we hypothesise that it will be particularly beneficial for heavy smokers who report the greatest difficulty with impulse control [4]. This is suggested by findings that stronger nicotine dependence is associated with poorer inhibitory control [44]. Thus, this is the first study to use the GNG task in a sample of individuals who have a Tobacco Use Disorder according to DSM-5 criteria and who wish to quit/reduce smoking.

As previous studies have found response inhibition training to be effective even when administered over the internet [36, 37], this study delivered the training paradigm online. This enabled the intervention to be accessible, convenient and cost-efficient for individuals and further contribute to reducing the burden on other treatment services and resources. The study is a randomised controlled trial (RCT) examining the efficacy of response inhibition training in reducing smoking in heavy dependent smokers. It is implemented in accordance with CONSORT guidelines, and involves collecting follow-up data from participants at 1 month and 3 months post-intervention.

### Primary hypotheses

Smokers who received smoking-related response inhibition training (INST program) would report significantly higher cessation rates compared to those in the active control condition at the end of the intervention, 1 month and 3 months post-intervention.Smokers who received smoking-related response inhibition training (INST program) would report significantly less cigarette consumption compared to smokers in the active control condition at the end of the intervention, 1 month and 3 months post-intervention.

### Secondary hypotheses

Smokers who received smoking-related response inhibition training (INST program) would report significantly less craving for cigarettes compared to smokers in the active control condition at the end of the intervention and 1 month and 3 months post-intervention.Smokers who received smoking-related response inhibition training (INST program) would report significantly lower levels of nicotine dependence compared to smokers in the active control condition at the end of the intervention and 1 month and 3 months post-intervention.

### Predictor/moderator hypotheses

Individuals reporting high levels of impulsivity would report significantly improved outcomes from the intervention training compared to those with lower levels of impulsivity^.^Individuals who completed a greater number of sessions (i.e., dose) would report significantly improved outcomes from the intervention training compared to those who completed less sessions.

### Mediator hypotheses

The effects of INST training on level of smoking would be mediated by devaluation of smoking stimuli as measured by a devaluation of smoking images task.The effects of INST training on level of smoking would be mediated by an independent measure of response inhibition (SST).

The following exploratory question was proposed:Do smokers who receive smoking-related response inhibition training (INST program) report significantly higher levels of self-confidence and motivation to quit smoking compared to smokers in the active control condition at the end of the intervention, 1 month and 3 months post-intervention.

## Methods/design

### Design

This is a 2-group parallel-block double-blind randomised controlled trial testing the efficacy of an intervention compared to an active control training. The intervention training is a smoking version of the food GNG training task in Lawrence et al. [36]. The active control training is similar to the control training in Lawrence et al. [36], with no-go training to household items. The Deakin University Human Research Ethics Committee (DUHREC) reviewed and approved all relevant study materials (Project ID: 2015–298). The trial was registered with the Australian New Zealand Clinical Trials Registry (Trial ID: ACTRN12617000252314; see Additional file 1: Table S1 for items from the World Health Organisation Data Set as per Spirit Guidelines). No study protocol amendments were made once the trial commenced and this protocol was originally submitted to this journal 1 November 2017.

### Procedure

The following sections describe the study procedure. See Table 1 for an overview.

#### Initial screening

Participants were adult smokers aged between 18 and 60 years, recruited through social media and advertisements in Victoria, Australia who had a desire to quit smoking.

#### Inclusion criteria

Aged between 18 and 60 years.Smoke, on average, a minimum of 10 cigarettes per day for the last 12 months.Meet criteria for moderate or above Tobacco Use Disorder defined by the DSM-5 [45].Be motivated to make a quit attempt during the training stage of the intervention.Completed at least Year 9 (or equivalent) schooling.Have computer and internet access during the intervention phase of the study.

#### Exclusion criteria

Primarily uses electronic cigarettes on a daily basis.Non-smoking period of 2 weeks or more in the past 3 months.Currently using anti-craving medication.Using nicotine-replacement therapy during the intervention period.Self-reported problematic alcohol or drug(s) use other than tobacco.Reported a traumatic or acquired brain injury or a loss of consciousness for more than 30 min.Reported current use of psychotropic medication such as anti-depressant, anti-psychotic and/or anxiolytic medication.

Interested participants were invited to contact the research team via email. They were screened over the phone/online to determine their eligibility. Participants who met the inclusion criteria were invited to participate in the study and attended a face to face interview in order to sign the consent form, collect baseline measures and participate in the first online training session.

#### Baseline assessment (T1)

At the beginning of the baseline interview session, participants read the plain language statement and if in agreement signed the consent form. They were requested to report any adverse events or consequences which will be reported in the flow chart of the primary outcomes paper. They were informed that they were able to withdraw from the study at any time. They were asked to indicate whether they would like to receive a summary of the trial findings following completion of data analyses. Participants were informed that they would receive one of two brain training tasks as the aim of the study was to investigate which one was more effective. While they were informed that the task incorporated a “variety of visual images”, the types of images were not specified to prevent participants from identifying if they were in the control group and hence we propose that participants were likely blind to the nature of the intervention and whether they were randomised to an active condition.

Participants completed a battery of questionnaires (outlined in Table 1), and completed ratings of their craving, motivation and self-efficacy. Following the completion of the questionnaires, participants completed ratings of stimulus evaluation test and a smoking stop signal task (SST), an independent measure of response inhibition separate to the response inhibition training.

**Table 1 Tab1:** SPIRIT Flow Diagram of the schedule for participants and data collection for the INST study

		STUDY PERIOD					
				Follow-Up Period			
	Enrolment	Baseline (T1) and Allocation	Training Period	Post-Intervention (T2)	1-Month Post-Intervention (T3)	3-Months Post-Intervention (T4)	Close-out
TIMEPOINT	*-t* _*1*_	*t* _*0*_ *-t* _*1*_	*t* _*2*_ *– t* _*14*_	*t* _*15*_	*t* _*45*_	*t* _*105*_	*t* _*x*_
ENROLMENT:							
Eligibility screen	X						
Informed consent	X	X					
*Obtain Contact Information*	X	X					
Allocation		X					
INTERVENTIONS:							
*INST intervention*		X	X				
*Control training*		X	X				
ASSESSMENTS:							
*Demographic Questions*		X					
*TLFB*		X		X	X	X	
*FTND*		X		X	X	X	
*DASS*		X		X	X	X	
*AUDIT*		X				X	
*BIS-11*		X		X	X	X	
*Stimulus Evaluation Test*		X		X	X	X	
*SST*		X		X		X	
*Craving Rating*		X	X	X	X	X	
*Motivation Rating*		X		X	X	X	
*Confidence Rating*		X		X	X	X	
*Time of last cigarette*		X	X				
CLOSE-OUT:							X
*Data-analysis*							X
*Debriefing of participants*							X
*Documentation and Dissemination of Findings*							X

t refers to days (from t_1_ onwards). *TLFB* Timeline Follow-Back interview, *FTND* Fagerström Test of Nicotine Dependence, *DASS* Depression Anxiety and Stress Scale, *AUDIT* Alcohol Use Disorders Identification Test, *BIS-11* Barrett Impulsiveness Scale, *SST* Stop Signal Task

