#### Randomisation

Immediately following the completion of the baseline assessment, participants began the online training task. Participants were automatically randomised to either the intervention or the control training task via a pre-computed randomisation procedure. A permuted block randomisation procedure was utilised [46] whereby participants were allocated to the intervention or control group through the use of a randomly generated number. The permuted blocks were organised in groups of ten, the details of which were not known by investigators involved with the administration of the trial. The use of the permuted block randomisation process ensures that intervention group numbers will be balanced at the end of each block and is thus the recommended process in studies with smaller samples.

Upon finishing this task participants were instructed to complete the online training task once per day for the next 13 days, totalling 14 sessions. They were asked to rate their smoking craving level before and after each training session. Twice per week, participants were sent text reminders to complete the training. All data from the online training task and outcome measures were securely stored on the Deakin University server and linked to an anonymous participant ID number such that only de-identified data were available to researchers. The data was checked for training task performance accuracy and participant adherence to the training protocol by a research assistant who was independent from investigators and not involved in data collection or analyses.

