#### Post-intervention (T2)

At the completion of the two-week intervention period, participants are contacted via phone by a researcher naïve to the group randomisation (i.e. a different researcher to the one who conducted the baseline interview). They receive a text message reminder 24-h prior to confirm the time of the phone call. During these phone interviews, participants are asked to provide details about their use of cigarettes and nicotine replacement therapies or anti-craving medications over the previous 2 weeks. At the conclusion of this interview, participants are emailed a link to complete the same battery of questionnaires, ratings of their craving, motivation and self-efficacy and SST (completed last) as completed at baseline (T1).

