#### One-month and three-months follow-up (T3 and T4)

Follow-up at 1 month (T3) and 3 months (T4) are conducted in the same manner as T2. The two follow-up time points are identical with the exception that the SST was not completed at T3 only in T4 to reduce participant burden. At the completion of each time point, participants were mailed a $20 gift card. At the conclusion of the data collection period, participants in the control group are offered the opportunity to complete the smoking-related response inhibition training.

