#### *Depression, Anxiety and Stress Scale (DASS-21)* [55]

The DASS-21 is a 21-item measure consisting of three subscales: depression, anxiety, and stress. Participants are asked to use a four-point Likert scale to rate the extent to which they have experienced the state described over the past week. The DASS has excellent internal consistency for the total scale (α = .97), and each subscale (Depression = .96; Anxiety = .92; Stress = .95) has high test-retest reliability and acceptable construct and convergent validity [56].

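### As described, adverse events are captured only by a request to participants at baseline and reported only in the flow chart, so harms may be under-counted and poorly characterised.

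*Protocol article*

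**What the plan says.** The only statement on adverse events is in the Protocol article, Baseline assessment (T1): "They were requested to report any adverse events or consequences which will be reported in the flow chart of the primary outcomes paper". That paragraph opens with the consent step: "At the beginning of the baseline interview session, participants read the plain language statement and if in agreement signed the consent form". Training comes later, under Randomisation: "Immediately following the completion of the baseline assessment, participants began the online training task".

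The section Post-intervention (T2) describes what the call covers: "participants are asked to provide details about their use of cigarettes and nicotine replacement therapies or anti-craving medications over the previous 2 weeks". The caller is a researcher who does not know the allocation. For the later calls: "Follow-up at 1 month (T3) and 3 months (T4) are conducted in the same manner as T2", with the stop signal task left out at one month as the only stated difference.

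The Measures section refers to Table 1 as the list of measures at each assessment point. The table has no adverse-event row. It does schedule the DASS at T1, T2, T3 and T4. The article describes that scale as follows: "The DASS-21 is a 21-item measure consisting of three subscales: depression, anxiety, and stress". Participants "rate the extent to which they have experienced the state described over the past week". The Analysis plan names analyses for smoking, craving, dependence, moderators, mediators, confidence, motivation and training performance. It names none for adverse events or for the DASS-21.

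**The concern.** The article states a method of collection and a place of reporting, and both are weak.

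- **Collection.** A request made once, before anyone has been exposed to the training, leaves it to the participant to recognise an event, remember the request and volunteer the event. Table 1 puts the last contact at day 105. Spontaneous reporting is generally less complete than asking.
- **Reporting.** A flow chart follows numbers of participants through the trial. It suits events that lead to withdrawal. It has no natural place for the nature and severity of an event in someone who carries on.

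Harm is not far-fetched here. The inclusion criteria require motivation to attempt to quit during training, and participants are asked to train preferably while craving. Only the intervention arm trains with smoking images, so any effect on craving or mood could differ by arm. The Discussion presents the training as simple, low-cost and easily accessible. A near-empty adverse-event count obtained passively could then be read as evidence of safety.

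**Working it through.** The article states no figure on this point, so there is nothing to reproduce. The check sets the passages side by side.

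1. **Order of events.** Request at the T1 session, then baseline measures, then randomisation and first training session. The only described elicitation therefore precedes all exposure.
2. **Follow-up contacts.** There are three: T2 (day 15), T3 (day 45) and T4 (day 105). The described content of T2 is cigarettes, nicotine replacement and anti-craving medication, followed by an emailed battery. T3 and T4 follow T2. Adverse-event items described: none.
3. **Table 1.** It is detailed enough to list the time of the last cigarette and the debriefing of participants. Adverse-event rows: none.
4. **Place of reporting.** One is named, the flow chart. A split by arm, event type, severity and denominator are not mentioned.
5. **Systematic data bearing on mood.** The DASS-21 is collected in both arms at four time points. Named analyses: none.
6. **Exposure that differs by arm.** 9 smoking images × 6 blocks = 54 presentations per session; 54 × 14 sessions = 756 in the intervention arm if every session is completed. In the control arm's training: 0.

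Items 1 to 4 agree with one another: as described, capture is spontaneous.

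**Illustration of direction only.** The event rates and capture shares below are assumptions; the article gives neither. Inputs: 150 / 2 = 75 per arm from the sample target, equal capture share c in both arms, two-sided 5% test. Expected reported count = 75 × rate × c. With p₁ and p₂ the reported rates (true rate × c) and p̄ their mean:

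power = Φ[(|p₁ − p₂| − 1.96·√(2p̄(1 − p̄)/75)) / √((p₁(1 − p₁) + p₂(1 − p₂))/75)]

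| True rates (assumed) | Capture c (assumed) | Expected reported counts | Power |
|---|---|---|---|
| 10% v 20% | 100% | 7.5 v 15.0 | 0.40 |
| 10% v 20% | 50% | 3.75 v 7.5 | 0.21 |
| 10% v 20% | 25% | 1.9 v 3.75 | 0.12 |
| 10% v 30% | 100% | 7.5 v 22.5 | 0.87 |
| 10% v 30% | 50% | 3.75 v 11.25 | 0.53 |
| 10% v 30% | 25% | 1.9 v 5.6 | 0.29 |

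Worked line (10% v 20%, c = 50%): p₁ = 0.05, p₂ = 0.10, p̄ = 0.075. The first root is √0.00185 = 0.0430 and the second is √0.001833 = 0.0428. Then (0.05 − 1.96 × 0.0430)/0.0428 = −0.80, and Φ(−0.80) = 0.21.

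Incomplete capture lowers the counts and weakens a comparison between arms even when it is equal in both. The table does not show that capture is incomplete in this trial.

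**The case against.** The strongest reply is that this is a condensed article. Call scripts and adverse-event forms normally sit in the full protocol, and the T2 section does not say that the call is limited to the topics it lists. That stands. A reader might infer that the follow-up callers make no enquiry about harms; the article supports only that none is described.

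Three further inferences also go too far.

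- **That an event counts only if the participant makes contact.** The trial itself calls participants three times, and the request sets no end date, so an event can be volunteered on a call.
- **That harms will not be visible by arm.** The trial has two arms and says that it follows CONSORT, so its flow chart would normally be split by arm. What is absent is a stated tabulation or comparison.
- **That harms will be under-counted.** Nothing in the article shows this. It can be said only that they may be.

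It is also fair to say that the DASS-21 is never called a safety measure, that analysis of an extra scale is ordinary SAP content, and that the article identifies no expected harm from a session of about 10 minutes of key-pressing. A question on the calls also cannot reach people who no longer answer them.

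The reply does not remove the point. The article chose to describe the method, the call content and the list of measures, and all three fit spontaneous reporting. The flow chart is named outright, so that part does not rest on silence.

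**Conclusion.** The point holds in a limited form. Described capture is a single request before training, with no adverse-event item in the described calls or in Table 1, and the flow chart is the only named place of reporting. Events may be missed. Type and severity in participants who continue may go unreported. The one systematic mood measure has no stated comparison by arm.

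The size of any under-count is unknown and cannot be derived from the article; the illustrative counts rest wholly on assumed rates. The conclusion assumes that the described call content and Table 1 reflect what is done, and a call script with an adverse-event question would remove the part on collection. No sample size, error rate or efficacy analysis is affected. This is a worthwhile improvement to harm ascertainment, not a threat to the primary result.

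**What to change.** - **Collection.** Add one open, identically worded adverse-event question to the T2, T3 and T4 calls, asked by the allocation-naive caller, or confirm that the call script already has one. Add the item to Table 1.
- **Reporting.** Give events by arm in a short harms table with type, severity and denominator, whether or not the participant continued.
- **DASS-21.** Pre-specify a baseline-adjusted summary of the three subscales by arm at T2 to T4.
- **If the calls are complete.** The table and the DASS-21 summary are still possible. State in the limitations that capture was passive, which the Discussion does not now do, and do not infer safety from a low count.

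The cost is one question on calls already scheduled, one table and one analysis of data already collected. Asking will raise the count of minor events in both arms. It will also not reach participants lost to follow-up, whom the Power analysis section puts at about 25%, so the harms table should show how many in each arm were asked at each time point.
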